## Methods

### Study Setting

This is a study of an IBI in French. We will recruit participants in Switzerland, but participation will be open to French-speaking people across the world.

### Design and Procedure

This study is a monocentric, single-blinded, 2-arm RCT comparing the efficacy of 2 versions of an IBI—namely LIVIA 1 and LIVIA 2.0—aimed at relieving distress and augmenting the well-being of people suffering from prolonged grief symptoms. There will be three measurement points: a pretest (T0), posttest (T1), and follow-up (T2). The flowchart of the study design is presented in Figure 1.

This self-help intervention is embedded in a larger project on life-span vulnerabilities and strengths conducted by the LIVES Centre [40].

**Figure 1 figure1:**
[figure not shown]
Flowchart of the study design. T0: assessment at baseline; T1: assessment at posttest; T2: assessment at follow-up.

### Study Conditions

#### LIVIA 1: Control Condition

LIVIA 1 is a self-help intervention for coping with prolonged grief symptoms after the death of a loved one or romantic separation/divorce, developed at the University of Bern by Brodbeck and colleagues [25]. Participants are encouraged to work through 1 session per week and complete the exercises provided. Each session takes approximately 60 minutes to complete. The sessions must be completed in the prescribed order. Details of the session contents can be found elsewhere [25].

#### LIVIA 2.0: Experimental Condition

LIVIA 2.0 is a psychological IBI composed of 10 sessions (see Table 1). These include an introductory session, a closing session, and 8 sessions in between belonging to 4 modules. Theoretically anchored in the DPM [30,31], each module comprises a session focused on loss and another on restoration. The modules have the following main themes: cognitions, emotions, behaviors, and identity. The sessions involving these modules are composed of psychoeducational information and exercises. In each session, participants can choose between 3 variants of the exercise (eg, some exercises vary in their themes or length). They are expected to complete 1 exercise per session but can complete all 3 available exercises if they wish to. LIVIA 2.0 also contains texts, audio and video files, and interactive quizzes.

**Table 1 table1:** Summary of the sessions and main content of LIVIA 2.0^a^.

Session	Module	Theme	Content
1	Introduction	Psychoeducation; assessment of resources and goals	Information about the self-help intervention, grief reactions, predictors, and treatment of complicated grief; assessment of individual resources and goals in pursuing the intervention
2	Cognition-focused	Loss-oriented session	Information about the impact of negative thoughts on well-being and the typical negative thoughts experienced during difficult grief; cognitive restructuration exercises
3	Cognition-focused	Restoration-oriented session	Information about secondary stressors and related thoughts; importance of building positive thoughts as resources; exercise to promote focus on positive aspects of one’s own life
4	Emotion-focused	Loss-oriented session	Information about the central role of emotions in the grieving process; assessment of own emotional state; self-compassion exercises
5	Emotion-focused	Restoration-oriented session	Importance of experiencing positive emotions, even if only briefly; hypnosis-like exercises to promote positive emotions
6	Behavior-focused	Loss-oriented session	Information about the typical vicious circle of avoidance in grief and the importance of confronting the avoided situations; confrontation exercises
7	Behavior-focused	Restoration-oriented session	Importance of behavioral activation in line with one’s own values; assessment of values; preparation of behavioral activation in line with one’s own values
8	Identity-focused	Loss-oriented session	Psychoeducation about identity formation and the way it is affected by grief; exercise aimed at revisiting memories and the relationship with the lost person; developing an independent sense of identity
9	Identity-focused	Restoration-oriented session	Psychoeducation about the importance of autobiographical memory for the individual's sense of self and ability to generate images of future events; exercise aimed at focusing on specific adaptive autobiographical memories and future projections to foster an independent sense of identity
10	Conclusion	Assessment of the individual’s experience of the intervention; relapse prevention	Promoting reflection on one’s own journey through the program (what was learned, what still needs to be done); identification of vulnerable moments and strategies to deal with the latter

^a^Modules 2 to 9 can be completed in the order chosen by the participants.

#### Navigation in the LIVIA 2.0 Program

The participants will first complete the introduction module. In this module, they will answer a questionnaire for allowing the program to automatically suggest an order of completion for the main modules (sessions 2 to 9, see Table 1), based on each participant’s priorities (eg, “It is important for me to avoid being taken over by negative thoughts” or “It is important for me to experience more positive emotions”). Nevertheless, participants will be able to choose the completion order freely. Each module consists of a (1) short introduction, (2) loss-related session, and (3) restauration-related session. Participants will mandatorily complete the module in this order. Once they have completed the 4 modules, they will complete the program with the conclusion session.

The following are the rules governing content access: (1) Once a session is opened, only that session is available for the next 7 days. After that, the following session is available, or if starting a new module, participants can choose the next module they wish to work on. (2) Within a session, participants can only access the content of that session or content that has already been completed. (3) Once they have reached the end of a session within a module, they can choose to do another exercise. (4) At the end of the intervention (12 weeks after starting it), they will have access to all the content.

#### Additional Resources

To assist participants as they complete the program, a toolbox will be provided with the content shown in Textbox 1.

Toolbox provided to the participants during the program.
**Favorites**
Participants will be able to add parts of the program that they particularly appreciate to their favorites.
**Individual resources of the participant**
Participants can access the assessment of their personal resources with AERES (a self-assessment scale for resources) during the first session (Bellier-Teichmann et al [20]).
**Soothing techniques for emotionally difficult times**
Short exercises, such as breathing exercises or tools to anchor attention in the present moment, will be available.
**Key scientific references**
We will provide the main references of the content of each session so that participants may deepen their knowledge on a specific domain, should they wish to.
**Automated emails**
To encourage participation, emails will automatically be sent (1) when a new session becomes available and (2) if the participant has not accessed the program for 7 consecutive days.

### Assignment of Interventions

To assign participants to the LIVIA 2.0 (experimental) or LIVIA 1 (control) condition, we will use the randomization module in REDCap (Research Electronic Data Capture [41,42]), which will automatically generate a 1:1 randomization. We will apply a single-blinded randomization strategy stratified according to the gender and loss type (bereavement vs separation) of the participants. Due to the nature of the study, double-blinded randomization is not possible.

### Participants

#### Sample Size

We will conduct a power analysis with G*Power (Version 3.1.9.2 [43]) for ANOVA of repeated measures involving within-between interactions that would enable us to compare the efficacy of the 2 interventions. Based on a probability level of 0.05 and a power of 0.8, to detect a small effect size of *f* =0.1 (as we expect small differences between the 2 programs), a sample size of 164 participants is needed. Expecting a dropout rate of 30% at the 3-month follow-up, we aim to have 234 participants at posttest.

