**Methods:**

Outcomes will be assessed at pretest, posttest (12 weeks later), and follow-up (24 weeks later). We will recruit 234 participants through a variety of means, including social media and contacts with the press. Primary outcomes are grief symptoms, depressive symptoms, and eudemonic well-being. Secondary outcomes are anxiety symptoms, grief coping strategies, aspects related to self-identity reorganization, and program satisfaction. LIVIA 2.0 participants will additionally undergo a weekly mood and grief symptom monitoring, allowing us to explore the short-term efficacy of the sessions.

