### Statistical Analysis

Primary analyses will be performed using SPSS (IBM Corporation) and R (R Foundation for Statistical Computing) after the participants complete the study. Primary follow-up analyses will be conducted 3 months later. Intermediate analyses during data collection will be done. We will perform intention-to-treat analyses [70]. We will develop multilevel mixed effects models with repeated measures data in SPSS to evaluate the efficacy of LIVIA 2.0 compared to LIVIA 1 and the stability of the effects. These models have the advantages of considering the dependency of the data and accounting for the correlation of repeated measures within individuals. Moreover, they rely on all available data of every participant and estimate parameters of missing values [71].

We will explore the potential moderating effect of different variables on the intervention effects by conducting analyses of covariance for repeated measures. To explore the short-term efficacy of each module, we will use multilevel modeling whereby each participant’s monitoring data are nested within participants. These analyses will be conducted with Mplus [72] or R. Additionally, we will analyze qualitatively the satisfaction questionnaire using the thematic content analysis method [73]. Finally, we will analyze the semantic content of the exercises included in LIVIA 2.0 [39] and test if some categories (eg, “we-talk”) are associated with the efficacy of the program. We will rely on a significance level of a 2-sided *α*=.05 or smaller. We will use the Bonferroni correction to adjust for multiple testing.

To handle missing data and dropouts, we will conduct the analyses relying on the intention-to-treat paradigm. We will first analyze the magnitude of missing data, explore the missing data patterns, and determine the pattern of missing data (missing completely at random, missing at random, and not missing at random). If the missing mechanism is missing at random, we will use multilevel regression analyses, which allow for nonindependent observations and for different numbers of measurement points per participant and are thus less sensitive to missing data [71].

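### The sample size is powered at an undivided alpha of .05, but three primary outcomes and a planned Bonferroni correction imply about 67% power per outcome on the protocol's own complete-case basis

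*Protocol article*

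**What the plan says.** The Sample Size section describes a G*Power calculation "for ANOVA of repeated measures involving within-between interactions that would enable us to compare the efficacy of the 2 interventions". Its inputs are given as "Based on a probability level of 0.05 and a power of 0.8", with a small effect of f = 0.1, and its result is that "a sample size of 164 participants is needed". Loss is then added: "Expecting a dropout rate of 30% at the 3-month follow-up, we aim to have 234 participants at posttest". Neither several outcomes nor a divided alpha is mentioned.

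The abstract states: "Primary outcomes are grief symptoms, depressive symptoms, and eudemonic well-being". The Primary Outcome Measures section gives one instrument for each and does not rank them. The Objectives section expects LIVIA 2.0 to be superior on every outcome.

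The Statistical Analysis section sets a two-sided level of .05 or smaller and adds: "We will use the Bonferroni correction to adjust for multiple testing". It does not say which tests form the family. The efficacy analysis is an intention-to-treat multilevel mixed model that uses whatever data each participant provides.

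**The concern.** The sizing alpha and the testing alpha are both stated, and they differ. A correction promised without qualification, beside three unranked primary outcomes, most naturally applies at least to those three. Each would then be tested at a stricter level than the one that produced 164.

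The control is an active program that has already been tested, and the protocol itself expects only small differences. A non-significant result on one or more primary outcomes is therefore quite possible. Readers would weigh it against a stated miss rate of about 1 in 5 per outcome. On the protocol's own sizing basis, the rate under the correction is about 1 in 3.

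**Working it through.** **Inputs from the article.** Two arms, 1:1; three measurement points (T0, T1, T2); f = 0.1; alpha .05; power 0.8; 164 before loss; 30% loss; 234 after inflation; three primary outcomes; Bonferroni.

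**Assumed.** Correlation between repeated measures rho = 0.5, and sphericity (epsilon = 1). The article gives neither.

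**Step 1. Reproduce 164.** For the within-between interaction with k = 2 groups and m = 3 times:

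- noncentrality λ = N·m·f²/(1 − rho)
- df1 = (k − 1)(m − 1) = 2
- df2 = (N − k)(m − 1)

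At N = 164, λ = 164 × 3 × 0.01/0.5 = 9.84 and df2 = 324. Power at .05 is 0.805. At N = 162 it is 0.7998, so 164 is the smallest even N that reaches 80%. Other settings do not reproduce it: m = 2 gives 200, m = 4 gives 138, rho = 0.3 gives 228 and rho = 0.6 gives 130. Inflation: 164/0.7 = 234.3, against the stated 234.

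**Step 2. Same calculation at the corrected alpha.** With λ and the degrees of freedom unchanged:

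| Tests in the family | Alpha | Power, 164 completers |
|---|---|---|
| 1 | .05 | 0.805 |
| 2 | .025 | 0.718 |
| 3 | .0167 | 0.665 |

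At .0167, 164 completers have 80% power for f of about 0.114 (0.803 at 0.114; 0.794 at 0.113). If sphericity fails with epsilon = 0.75, the 0.665 falls to 0.555.

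**Step 3. Allow for partial data.** The mixed model would also use data from the 234 − 164 = 70 people without T2. Let d be the between-arm difference at T0, T1 and T2 in SD units, scaled so that Σ(d_t − mean d)²/12 = 0.01, which is f = 0.1. Let C take the changes from T0, and let V be the generalized least squares covariance of the estimated differences. Then λ = (Cd)′(CVC′)⁻¹(Cd). With complete data this returns 9.84 for 164 people. Taking data as missing at random, each cell below gives λ and then power at .0167:

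| Effect, T1 : T2 | All 70 have T1 | 35 have T1, 35 do not | None has T1 |
|---|---|---|---|
| Equal (1 : 1) | 13.07, 0.81 | 12.04, 0.77 | 10.93, 0.72 |
| Growing (0.5 : 1) | 11.14, 0.73 | 10.91, 0.72 | 10.66, 0.71 |
| Fading (1 : 0.5) | 14.04, 0.85 | 12.41, 0.79 | 10.66, 0.71 |

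The range is about 0.71 to 0.85. An effect present only at T2 would sit slightly lower (λ about 10.1 to 10.2, power about 0.68). With no loss at all, 234 people give λ = 234 × 3 × 0.01/0.5 = 14.04 and power 0.847, which is the ceiling.

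The first column follows the Sample Size wording, which places the 234 at posttest. The other two follow the abstract, where 234 is the number recruited.

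**The case against.** **The 67% is not the power of the planned analysis.** This is the strongest objection, and it stands. The 0.665 counts only 164 complete cases, whereas the mixed model uses partial records. The gain is not trivial: roughly 5 to 18 points across the cases in the table, enough in some of them to restore 80%. The 67% therefore describes the protocol's own sizing basis, not the final model.

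**The Bonferroni family is not spelled out.** This is also true. The sentence closes a paragraph that begins with moderators and goes on to module-level and semantic analyses, while the efficacy model is described in the paragraph before. The family could be left to an analysis plan that is not shown. But the sentence carries no restriction, and three unranked primary outcomes are its natural minimum. If it was not meant to cover them, three independent tests at .05 would carry a familywise error of 1 − 0.95³ = 0.143. The text needs a decision either way.

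**The chance of at least one significant primary outcome stays high.** It is 1 − (1 − 0.665)³ = 0.96 if the outcomes are independent. That does not answer the point, because the Objectives section claims superiority on every outcome.

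**Bonferroni is a valid method.** Agreed. Choosing another procedure is optional and is not the substance of the point.

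**Conclusion.** The point holds as an inconsistency between two sections. It is not an arithmetic error: 164 is right for one test at .05. With the three primary outcomes as the family, power per outcome is about 67% on the protocol's complete-case basis, and roughly 71% to 85% under the planned mixed model. These figures rest on rho = 0.5, sphericity, f = 0.1 for each outcome and, for the mixed model, data missing at random.

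Two stronger readings are tempting, and the documents do not support them:

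- A reader might infer that no primary outcome can have the stated power. Partial data can bring power back to 80% or slightly above, so this is not established.
- A reader might infer that recruitment must rise, since 80% at .0167 needs 212 completers and 212/0.7 = 303. That requirement ignores the partial data that the planned model would use.

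Nor should the power of the two-degree-of-freedom interaction be read as the power of separate T1 and T2 comparisons. Those are different tests.

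**What to change.** 1. In Statistical Analysis, state that the Bonferroni family is the three primary outcomes, each tested by the group-by-time interaction used for sizing, at .05/3 = .0167.
2. In Sample Size, restate the power at that alpha: about 67% per outcome on 164 completers, or 80% for f of about 0.114, and higher with partial data. Give the assumed correlation, sphericity and dropout timing.
3. If a single contrast is chosen instead, recompute the power for it, because the figures above do not carry over. For example, with 164 completers, equal effects at T1 and T2 and f = 0.1, the scaled difference is √(0.12 × 3/2) = 0.424. For the change to T1 alone, the standard error is √(2 × 1/82) = 0.156, so z = 2.72 and power at .0167 is about 0.63. For the change to the mean of T1 and T2, it is √(2 × 0.75/82) = 0.135, so z = 3.14 and power is about 0.77.
4. Optionally, use Holm, which gives the same familywise control and is never less powerful, and label secondary and moderator tests as exploratory.

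This changes wording only and needs no extra participants. The cost is a less favourable stated power. It should be settled before outcome data are analysed; the Results section says that none had been collected at submission.

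### The sample size is described as powered for small differences between the programs, but f = 0.1 for the group-by-time interaction is a between-arm difference of about 0.42 to 0.49 SD

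*Protocol article*

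**What the plan says.** The Sample Size section names the test behind the calculation, a G*Power analysis "for ANOVA of repeated measures involving within-between interactions that would enable us to compare the efficacy of the 2 interventions". The error rates are given as "Based on a probability level of 0.05 and a power of 0.8". The effect size is f = 0.1, labelled small, with the justification "as we expect small differences between the 2 programs), a sample size of 164 participants is needed". The 164 is then raised to 234 for an expected 30% dropout.

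The design inputs come from elsewhere in the article. Design and Procedure gives two arms ("This study is a monocentric, single-blinded, 2-arm RCT") and three measurement points: pretest (T0), posttest (T1) and follow-up (T2). Assignment of Interventions gives equal allocation ("which will automatically generate a 1:1 randomization"). Statistical Analysis sets the level ("We will rely on a significance level of a 2-sided" alpha of .05 or smaller), plans mixed-effects models for repeated measures, and promises a Bonferroni correction. There are three primary outcomes.

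The article does not state the correlation between measurements or the number of measurements entered in G*Power, and it does not translate f into a difference between arms in SDs or scale points.

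**The concern.** The label small for f = 0.1 belongs to a simple comparison of two group means, where f is half the standardised difference and 0.1 therefore means 0.2 SD. In a within-between interaction, f measures the spread of the interaction cell effects. Those are what remains of the arm difference after its average over occasions is removed and the rest is split between two arms. The same f then stands for a much larger difference between arms.

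This matters because the comparator is an active program that the article describes as already shown to be effective. Small differences are the stated expectation, and superiority on all outcomes is a main hypothesis. A reader of the Sample Size section would conclude that the trial has an 80% chance of detecting a small advantage, and could give a non-significant result more weight against such an advantage than it can bear.

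**Working it through.** **1. Reproduce 164.** Inputs: k = 2 groups, m = 3 measurements, f = 0.1, alpha = 0.05, power 0.80 (all in the article); correlation rho = 0.5 and sphericity epsilon = 1 (not stated; assumed).

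- Noncentrality: lambda = f² × N × m / (1 − rho) = 0.01 × 164 × 3 / 0.5 = 9.84.
- Degrees of freedom: (k − 1)(m − 1) = 2 and (N − k)(m − 1) = 324. The critical F is 3.02.
- Power is 0.805 at N = 164 and 0.7998 at N = 162, so the smallest total with equal arms is 164, as stated.

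Other settings with three measurements give different totals: 228 at rho 0.3, 130 at rho 0.6, 98 at rho 0.7, and about 486 under G*Power's 'as in SPSS' effect-size option. Two measurements give 200 at rho 0.5 and 160 at rho 0.6. They would give 164 at rho 0.59, but that is an unusual input and does not match the three measurement points.

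**2. Convert f to a difference between arms.** Let D be the arm difference in outcome SDs, with the arms equal at T0 because of randomisation. Centre the differences over the three occasions, halve them for the two arms, and take the root mean square.

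- Sustained, (0, D, D): cell effects are ±(−D/3, D/6, D/6). The mean square is (D²/9 + D²/36 + D²/36)/3 = D²/18. So f = D/√18, and f = 0.1 gives D = 0.424.
- At one occasion only, (0, D, 0) or (0, 0, D): the mean square is the same, so D = 0.424.
- Linear build-up, (0, D/2, D): cell effects are ±(−D/4, 0, D/4). The mean square is D²/24, so D = 0.490.

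This conversion does not depend on rho. Even with two measurements, (0, D) gives f = D/4 and D = 0.40.

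**3. Power for smaller differences, N = 164, rho = 0.5, 2-df interaction test.**

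| D | Profile | f | lambda | Power |
|---|---|---|---|---|
| 0.2 | sustained | 0.0471 | 2.19 | 24% |
| 0.2 | linear | 0.0408 | 1.64 | 19% |
| 0.3 | sustained | 0.0707 | 4.92 | 49% |
| 0.3 | linear | 0.0612 | 3.69 | 38% |

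Simulation of the same test (10,000 runs each) gave 80.4% at a sustained 0.424, 80.1% at a linear 0.49, 23.7% at a sustained 0.2 and 19.4% at a linear 0.2.

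**4. Sensitivity at D = 0.2.**

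- rho 0.3: 18% sustained, 15% linear. rho 0.7: 38% and 29%.
- Alpha 0.05/3 for three primary outcomes: 13% and 9%.
- All 234 analysed: 33% and 26%.

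**5. A single contrast from the mixed model.** For the mean of T1 and T2 adjusted for T0 at rho 0.5, the residual variance is 0.75 − 0.25 = 0.50. The standard error is √(0.50 × 2/82) = 0.110.

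- Sustained 0.2 SD: 0.2/0.110 = 1.81, power 44% (58% if all 234 were analysed).
- Sustained 0.424 SD: power 97%, against 80% for the interaction test.
- 0.424 SD at one occasion only: the average sees 0.212 SD and power is 48%, against 80% for the interaction test.
- Difference detectable with 80% power: 2.80 × 0.110 = 0.31 SD.

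**The case against.** The strongest reply is that nothing is miscalculated. The 164 is correct for its inputs, 0.1 is the conventional small value of f, and the article never sets a target in SD units. The benchmark of 0.2 SD and the correlation of 0.5 are both supplied from outside the text. All of this stands, and for that reason the percentages are conditional. It does not rescue the claim: the stated reason for choosing f = 0.1 is an expectation about differences between the programs, and the conversion to 0.42–0.49 SD needs neither the benchmark nor the correlation.

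A second reply is that the planned analysis is a mixed model, with the ANOVA serving only to size the trial. This is fair, and a well-chosen contrast does better. At a sustained 0.2 SD it still reaches only 44%, or at most 58% with all 234 analysed.

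A reader might go further and infer that the omnibus test wastes power and must be replaced by an averaged, baseline-adjusted contrast with the stratification factors as covariates. The documents do not support that. The average gains for a sustained effect but loses when the effect is present at one occasion only, and the article asks about stability of effects over time. The choice of contrast and covariates is also detail that an article may leave to the full plan. Nor does any passage say that a null result will be read as excluding small differences; that is a risk of the wording, not a stated intention.

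**Conclusion.** The point holds as a misdescription of what the trial can detect. With 164 analysed, the sized test has 80% power at alpha 0.05 for about 0.42 SD between arms (sustained, or at one occasion) or 0.49 SD (linear). It does not have 80% power for a small difference in the ordinary two-group sense. If small means 0.2 SD, power is about 24% or 19% at a correlation of 0.5, and 15% to 38% over correlations of 0.3 to 0.7. No variant examined within that range of correlations comes near 80%.

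The conversion rests on the G*Power default definition of f, three measurements and arms equal at T0. The power figures also rest on the inferred correlation and the assumed 0.2 SD.

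It would be tempting to conclude that 164 is a wrong number or that the trial must grow. Neither follows. The arithmetic is right for its inputs, and the article fixes no minimum difference in SDs that the trial is obliged to detect.

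**What to change.** In the Sample Size section, remove the statement that the trial is powered for small differences between the programs. State instead that 164 analysed participants give 80% power at alpha 0.05 for about 0.42 SD between arms (sustained at T1 and T2, or at one of them) to 0.49 SD (building linearly to T2). Give the number of measurements and the correlation assumed; three and 0.5 reproduce the figure, and the authors should confirm them. Add a sentence acknowledging that a non-significant result would not rule out smaller differences.

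Naming a single averaged contrast as the primary test is optional. If it is adopted, quote its own detectable difference, about 0.31 SD at a correlation of 0.5 for a sustained effect, in place of 0.42–0.49 SD.

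The cost is a few sentences. No participants, measurements or data are added.

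### The figure of 234 is the number recruited in the abstract but the number present at posttest in the sample-size section, and the starting point of the 30% dropout is not stated

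*Protocol article*

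**What the plan says.** The Methods paragraph of the abstract gives a recruitment target: "We will recruit 234 participants through a variety of means". It places posttest 12 weeks after pretest and follow-up at 24 weeks.

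The Sample Size section plans for "ANOVA of repeated measures involving within-between interactions". The settings are "Based on a probability level of 0.05 and a power of 0.8", with an effect size of f = 0.1, and the result is 164 participants. It then continues: "Expecting a dropout rate of 30% at the 3-month follow-up, we aim to have 234 participants at posttest".

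The Recruitment section says that recruitment efforts go on until the desired number is reached, but gives no number. The Results section allows the recruitment period to be prolonged, again without a number.

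**The concern.** One figure is attached to two time points 12 weeks apart. Recruiting 234 and having 234 at T1 are compatible only with no loss at all during the self-help programme. The protocol does not expect that: its third main hypothesis is that the two programmes differ in dropouts, and the Statistical Analysis section plans for dropouts and missing data.

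The 30% is ambiguous in the same way. Taken literally, the sentence starts from 234 at posttest and loses 30% by the 3-month follow-up, which is a T1-to-T2 loss. Read with the abstract, the 30% looks like the total loss from T0 to T2.

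What depends on this is when recruitment stops and how many participants can be expected at T2. The article gives no loss rate between T0 and T1 that would connect the two statements.

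**Working it through.** **Inputs from the article.** Two arms, for which REDCap is used, "which will automatically generate a 1:1 randomization" (Assignment of Interventions); three measurement points, T0, T1 and T2 (Design and Procedure); f = 0.1, alpha 0.05, power 0.80, 164 needed, 30% dropout (Sample Size). The Statistical Analysis section uses a two-sided level; the interaction F test has no one-sided version, so this changes nothing here.

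**Inputs assumed.** The correlation between repeated measures (rho = 0.5) and the sphericity correction (epsilon = 1) are not stated. These values are the G*Power defaults.

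**Step 1: reproduce 164.** For the within-between interaction with k = 2 groups and m = 3 measurements:

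- noncentrality λ = N × m × f² / (1 − rho) = 164 × 3 × 0.01 / 0.5 = 9.84
- df1 = (k − 1)(m − 1) = 2
- df2 = (N − k)(m − 1) = 162 × 2 = 324
- power from the noncentral F distribution = 0.805

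Under these assumptions 164 is the smallest even N that reaches 0.80, so the stated figure is reproduced.

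**Step 2: reproduce 234.** 164 / 0.7 = 234.3, and 234 × 0.7 = 163.8. So 234 is the number before a 30% loss and 164 is the number after it.

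**Step 3: the readings.**

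- *A. 234 randomised, 30% lost in total by T2.* 234 × 0.7 = 163.8, about 164; power 0.80. The abstract is right and the word posttest is wrong.
- *B. 234 present at T1, 30% lost afterwards.* 234 × 0.7 = 163.8, about 164; power 0.80. The sample-size sentence is right, and the abstract's recruitment figure is too low by whatever is lost before T1.
- *C. 234 randomised (abstract) and 30% lost only after T1 (literal sample-size sentence).* The number at T2 is 234 × (1 − d) × 0.7, where d is the T0–T1 loss.

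**Step 4: the size of B and C.** No value of d is given, so a range is assumed. Power for C uses the Step 1 formula with the number at T2 as N. The recruitment needed for B is 234 / (1 − d), rounded up.

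| Assumed T0–T1 loss d | C: present at T1 | C: present at T2 | C: total loss by T2 | C: completer-based power | B: number to randomise |
|---|---|---|---|---|---|
| 5% | 222.3 | 155.6 (about 156) | 33.5% | 0.78 | 247 |
| 10% | 210.6 | 147.4 (about 147) | 37% | 0.76 | 260 |
| 20% | 187.2 | 131.0 (about 131) | 44% | 0.70 | 293 |
| 30% | 163.8 | 114.7 (about 115) | 51% | 0.64 | 335 |

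**The case against.** A reader might infer from the two statements that the trial will fall short of 164 at follow-up and is therefore underpowered. The documents do not support that. Readings A and B are each consistent in themselves, and each leaves about 164. A shortfall arises only in reading C, where the recruitment figure of one reading is combined with the dropout base of the other. Reading A is plausible: the article gives a single dropout rate, places it at the last assessment, and 164 / 0.7 matches the recruitment figure in the abstract.

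The powers in the table also count only participants still present at T2. The Statistical Analysis section plans intention-to-treat mixed models that use all available data, so people seen at T0 and T1 but not at T2 still contribute. The loss of power in the planned analysis would be somewhat smaller than shown. The 30% row, with more than half the sample lost by T2, is the end of an assumed range and not an expectation taken from the article.

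Two further points might be added to this one but do not belong to it. The difference between 234 and 235 is rounding: with 163 participants power is still 0.802. What a Bonferroni-adjusted level would do to power is a separate question.

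What stands is the inconsistency. The article attaches 234 to two time points, expects dropouts, and nowhere says which statement governs. The completer argument does not remove this, because the article's own sample-size calculation is a repeated-measures ANOVA inflated for dropout and should be coherent on those terms.

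**Conclusion.** The inconsistency is real and should be fixed. The calculation itself is sound: 164 is reproduced with rho = 0.5 and epsilon = 1, and the step to 234 is correct for a 30% loss. What is not fixed is the time point to which 234 belongs and the point from which the 30% is counted.

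The consequence is conditional. If the 30% is cumulative from T0, one word is wrong and power stays at 0.80. If 234 are randomised and the 30% falls only after T1, completer-based power runs from about 0.78 to 0.64 for assumed early losses of 5% to 30%, with a somewhat smaller effect on the planned mixed models. The text does not settle which case applies.

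**What to change.** State one number to be randomised, use it in both the abstract and the Sample Size section, and state the time point from which the 30% is counted. Only the sponsor can say which meaning was intended.

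- If total loss from T0 to T2 was meant, replace the reference to posttest with randomisation: 234 randomised, 30% lost by T2, about 164 remaining. The cost is one phrase; the abstract stays as it is.
- If 234 at posttest was meant, state the assumed T0–T1 loss. Then either give the matching recruitment figure (247, 260, 293 or 335 for assumed losses of 5%, 10%, 20% or 30%), or keep 234 randomised and restate the expected number at T2 and the power. The first option costs 13 to 101 additional participants over that range (247 − 234 to 335 − 234). The second costs no participants but means accepting and reporting lower power.

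The article reports that no data had been collected at submission and that recruitment might be prolonged, so at that stage either route was open.
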